#### Lung cancer screening outcomes

Results of participants’ LDCT scans are documented by each participating screening site using the standardized American College of Radiology (ACR) Lung Image Reporting and Data System (Lung-RADS) [58] of lung nodule identification, classification, and management. Lung-RADS categories range from 1 (negative), 2 (benign appearance), 3 (probably benign), and 4 (suspicious). Lung nodules categorized as category 1 and category 2 are classified as negative scans whereas category 3 and category 4 nodules are classified as positive scans. We also collect data on other incidental clinically significant or potentially significant abnormalities (i.e., S modifiers) and lung cancer diagnosis.

#### Site coordinator assessments

Data regarding SC demographics, their primary role at the lung cancer screening site, prior training as a tobacco treatment specialist, and smoking-related beliefs are collected at baseline. Baseline and follow-up assessments also include data regarding LDCT-LCS site characteristics (e.g., geographic region, patient volume, organizational priority for treating tobacco dependence, academic affiliation). We assess each site’s usual tobacco treatment practices and perceived barriers/facilitators of tobacco treatment implementation, the feasibility of implementing such processes, appropriateness (fit), and sustainability of these practices [51, 59]. These areas are also assessed during a semi-structured interview with site coordinators at the end of their participation. Interviews are recorded and transcribed for qualitative analysis.

#### PACT ancillary sub-study of SCs and Black participants

A semi-structured interview guide is used to conduct interviews with eligible Black patients who declined CASTL participation, and SCs who have screened at least 30 patients for study eligibility. The approximately 30 min interview covers topics such as barriers to tobacco treatment, prior experience with research, and reasons for tobacco treatment trial refusal [60]. The PACT semi-structured interview of SCs assesses attitudes as well as barriers, challenges, and facilitators of referring participants to the CASTL study.

#### Cost

The economic impact of the tobacco treatment components will be assessed by performing both cost and cost-effectiveness analysis. The goal of the cost analysis is to estimate the incremental costs associated with delivering tobacco treatment components in the context of LDCT-LCS. The primary endpoint of this analysis is the cost of each treatment component and the cost of each permutation of treatment components. The base-case cost analysis includes the costs of all resources consumed for the implementation and delivery of the tobacco treatment components. We will also examine costs and potential payment sources (e.g., health insurance benefits) from the provider (i.e., LDCT-LCS site) perspective, in order to estimate the net cost to screening sites that want to adopt the optimized treatment combination or individual components of it. Data sources for the cost analysis include SC treatment logs which document the delivery of treatment components and associated personnel time. Administrative and overhead costs will be estimated by each study site. The cost of medications (nicotine lozenges and patches) will be based on acquisition costs. In sensitivity analysis, we will examine a range of unit cost values for these items, reflecting the range of values reported in the medical literature and on pharmacy websites. Intervention cost estimates will include only the resources used in implementing and delivering the study interventions. Resources used solely for research purposes will be excluded.

Cost-effectiveness will be estimated as the incremental cost per additional participant with biochemically verified abstinence. This endpoint corresponds with the trial’s primary clinical endpoint and will facilitate comparison with other smoking cessation trials that estimate cost-effectiveness as cost per quit [61]. In addition to intervention costs, the numerator of the cost-effectiveness ratio will include the costs of smoking cessation supplies consumed after the study treatment period and other non-study tobacco treatment services received and the patient time and travel costs associated with these services. The use of additional tobacco treatments and time and travel costs will be reported by participants in the 3- and 6-month follow-up surveys. Incremental cost-effectiveness ratios will be estimated for all non-dominated intervention strategies, and uncertain parameters will be varied in sensitivity analysis across a range of plausible values.

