##### Nicotine lozenge [31, 32]

Participants randomized to this treatment component receive 6 cartons of 2 mg lozenges (81 units/carton) by mail, along with written instructions to use the lozenges to help manage acute nicotine withdrawal. Participants are instructed to use the NRT lozenges no more than every 1–2 h as needed and up to 20 lozenges per day during their initial session with the site coordinator for a period of 6 weeks.

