#### Statistical power and sample size considerations for the primary aim

Using the statistical power calculation computer programs designed specifically for MOST studies [64] and accounting for up to 20% attrition, the anticipated sample will afford an 85% statistical power (type I error at two-sided 5%), at an estimated minimal effect size of 0.20 in standard deviation units, what Cohen would consider a “small” effect in behavioral research [65]. The 0.20 minimal effect size represents the smallest main effect that can be supported by the proposed sample size in the MOST intervention components. For illustration, a difference between 20 and 12% abstinence rates, when converted by an arcsine transformation, corresponds to a Cohen’s *d* = 0.22.

*Aim 2. To estimate the cost and incremental cost-effectiveness of evidence-based tobacco treatment components, delivered alone and in combination.*

The base-case cost analysis will take a societal perspective, estimating all costs associated with treatment components delivered separately and in combination. We will conduct a separate cost analysis from the provider’s perspective. We will use standard methods [66] of incremental cost-effectiveness analysis to estimate the additional cost per quit achieved, where cost includes both intervention costs and 6-month downstream costs of related health care tobacco cessation services, and the effectiveness measure is defined by 7-day point prevalence abstinence at 6 months.

Given the primary focus of the trial on non-economic endpoints, and sample size requirements associated with these endpoints, formal hypothesis testing on the economic outcomes will not be conducted. Resource utilization and cost data are typically skewed, and therefore, the sample size of the trial may be insufficient to detect significant differences in costs between study arms [67]. The economic impact of the intervention will be evaluated using standard incremental cost-effectiveness analysis methods. For example, it is possible that several treatment combinations may yield comparable effectiveness in abstinence. If this happens, then the incremental cost per abstinence may be factored into this consideration. Sensitivity analysis will be conducted to assess the impact of assumptions and uncertainty on results and conclusions [66, 68]. This analytic approach is appropriate in economic studies that “piggyback” randomized trials [69].

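### On its literal wording, the cost-effectiveness numerator leaves out non-study NRT bought during the treatment period, so the incremental cost per quit of the NRT components can be biased

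*Protocol article*

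**What the plan says.** The Cost section builds the numerator of the cost-effectiveness ratio from three parts.

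- **Study intervention costs**, restricted as follows: "Intervention cost estimates will include only the resources used in implementing and delivering the study interventions".
- **Supplies**, with a time limit: "the numerator of the cost-effectiveness ratio will include the costs of smoking cessation supplies consumed after the study treatment period".
- **Services**, with no time limit, in the continuation of the same sentence: "and other non-study tobacco treatment services received and the patient time and travel costs associated with these services".

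On data, the section adds: "The use of additional tobacco treatments and time and travel costs will be reported by participants in the 3- and 6-month follow-up surveys".

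The Aim 2 paragraph of the analysis section says of the cost analysis: "The base-case cost analysis will take a societal perspective, estimating all costs associated with treatment components delivered separately and in combination". For the cost-effectiveness analysis it says that "cost includes both intervention costs and 6-month downstream costs of related health care tobacco cessation services". Effectiveness is 7-day point prevalence abstinence at 6 months.

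Under Nicotine lozenge, participants "receive 6 cartons of 2 mg lozenges (81 units/carton) by mail" and are told they may use "up to 20 lozenges per day during their initial session with the site coordinator for a period of 6 weeks".

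**The concern.** Abstinence is measured 6 months after randomization, so it reflects whatever participants used from the first day. The supplies item starts counting only when the study treatment period ends. Anything a participant buys before then can help produce a quit without appearing as a cost.

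The gap need not be equal across conditions. A participant given no NRT, but advised to quit and referred to the Quitline, may buy some; leaving that out makes the comparator look too cheap and the NRT components too expensive. A lozenge participant who runs out may buy more; leaving that out makes the lozenge look too cheap. At stake is the incremental cost per quit of patch and lozenge, which the Aim 2 paragraph says may be considered when several combinations have comparable abstinence.

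**Working it through.** **Step 1. Where could an in-period purchase enter?** Take NRT that a participant buys and uses in week 3.

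| Numerator item | Rule in the Cost section | Does the purchase count? |
|---|---|---|
| Intervention cost | Study-delivered resources only | No: the study did not supply it |
| Supplies | Used after the treatment period | No: used within it |
| Services, time and travel | Non-study services, undated | Not literally: it is a supply, and the sentence lists supplies separately |

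The Aim 2 definition adds downstream costs of cessation services, which does not restore in-period supplies.

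**Step 2. Who could buy?** In Table 1, conditions 1, 2, 9 and 10 include neither patch nor lozenge. All participants get cessation advice and a Quitline referral (Enhanced standard care). The exclusion for recent cessation medication (Patient eligibility) concerns the month before entry, not purchases after randomization.

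**Step 3. Can lozenge participants run out?** Inputs are from Nicotine lozenge.

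- Supplied: 6 × 81 = 486.
- Stated maximum over 6 weeks: 20 × 42 = 840.
- Difference: 840 − 486 = 354; the supply is 486/840 = 58% of the maximum.
- Supply lasts 486/20 = 24.3 days at the maximum.
- It lasts all 42 days at 486/42 = 11.6 a day or fewer.

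Running out is therefore possible on the article's own figures, though not inevitable. The patch is supplied for the full 6 weeks, so this mechanism concerns the lozenge only.

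**Step 4. Direction and possible size.** The article states no price, purchase rate or cost ratio, so there is no figure to reproduce and none can be corrected. What follows is an illustration on assumed values. Let one supplied lozenge course cost 1, and let bought product cost the same per unit. Let q be the share of participants without lozenge who buy NRT, f the fraction of a course they buy, u the share of lozenge participants who top up, and t the top-up as a fraction of a course.

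Product cost difference as counted = 1. With in-period purchases = 1 + u·t − q·f.

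At 15 a day, t = (15 × 42 − 486)/486 = 0.296. At 20 a day, t = 354/486 = 0.728. Assumed ranges: q 0 to 30%, f 0.25 to 1, u 0 to 30%, and use of 15 to 20 a day among those who top up.

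| Assumed values | With in-period purchases | Counted figure is |
|---|---|---|
| q = 0, u = 0 | 1.00 | unbiased |
| q = 0.30, f = 1, u = 0 | 1 − 0.30 = 0.70 | 0.30 too high |
| q = 0, u = 0.30, 20 a day | 1 + 0.30 × 0.728 = 1.22 | 0.22 too low |
| q = 0.30, f = 0.25, u = 0.10, 20 a day | 1 + 0.073 − 0.075 = 0.998 | almost unbiased |

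The control-side extreme is demanding. Half of the conditions without lozenge (3, 4, 11 and 12) receive patches. If only participants with no NRT buy, q = 0.30 requires 60% of those in conditions 1, 2, 9 and 10 to buy a full course. The figures cover product cost only, not staff time or the abstinence difference in the denominator.

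**The case against.** The strongest reply is that the exclusion is one reading and not a declared rule. The services item carries no dates. The next sentence has participants report additional tobacco treatments at 3 and 6 months, and Table 2 lists NRT use at both. The supplies clause may have been written only to pick up continued use once study product ends. This stands in part: it makes the exclusion less than certain, and it shows that the relevant reports are already planned. It does not remove the limit, because collecting a report is different from stating that it enters the numerator.

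A reader might infer that the article contradicts itself, since the base case is societal and covers all costs. That goes too far. The sentence describes the cost analysis and refers to costs associated with the treatment components delivered; a control participant's own NRT is not plainly such a cost. The two paragraphs fit poorly but do not conflict outright.

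A reader might also infer that cost is a fixed tie-breaker, so that the omission decides the recommended package. The Aim 2 paragraph says only, by way of example, that cost may be considered. Component selection rests on the Aim 1 model, and no formal tests are planned on economic outcomes.

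Planned sensitivity analyses vary unit costs and uncertain parameters. That does not add back a cost category that was never included.

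**Conclusion.** The concern holds as a defect of wording that can bias a secondary economic result. Followed literally, the Cost section leaves in-period non-study NRT out of every part of the numerator, while abstinence from the same weeks is credited.

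The documents do not support the stronger statement that the incremental cost of the NRT components is wrong. That would require purchases to occur, to differ by condition and not to cancel, and the article has no data on any of these. The illustrated span, from 0.30 of a lozenge course too high to 0.22 too low, depends wholly on the assumed purchase rates, quantities and equal unit prices. It shows that either sign is possible; it is not evidence of bias and not an error in cost per quit. The primary abstinence analysis is unaffected.

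The literal reading takes the treatment period to be the 6 weeks of NRT supply. The article does not define the term, and no separate criticism is made of that.

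**What to change.** In the Cost section, replace the limit to supplies used after the treatment period with all cessation supplies and services not provided by the study and used between randomization and the 6-month survey, in every condition. State that they are costed from the 3- and 6-month survey reports. In the Aim 2 paragraph, define cost over the same window in place of downstream services alone.

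This costs one sentence in each place and no new visits, since the 3-month survey falls after a 6-week course. The article does not show the survey items, so the team should confirm that they separate bought from study-supplied NRT well enough to cost it. The drawback is reliance on 3-month recall for early purchases.

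Separately, the lozenge quantity supplied and the stated maximum over 6 weeks do not match and are for the sponsor to reconcile. No change to either is proposed here.

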### Data analysis

#### Analytic strategies to address research aims

*Aim 1: To identify which of four evidence-based tobacco treatment components contribute to superior cessation endpoints among persons who currently smoke seeking lung cancer screening over and above enhanced standard care.*

In addition to descriptive statistics, a generalized hierarchical linear mixed effects modeling approach will be used to address the primary effectiveness aim. This approach will account for the nested structure of the data (i.e., patients nested within sites) via random intercepts and allow the use of a logit link function for the binary outcome of abstinence. With the factorial design of this study, a fully saturated model includes all four main component effects, 6 two-way interactions, 4 three-way interactions, and 1 four-way interaction.

The main analytic strategy involves a model simplification process. The saturated model will be fitted first. Next, model terms with a statistically reliable effect (by *p* < 0.05 in the type 3 analysis of variance table) will be retained. We envisage that some synergistic effects (interactions) will emerge and be deemed the optimized tobacco treatment package. All analyses will be guided by the intention-to-treat principle [62], in which participants with missing outcomes will be deemed non-abstinent, and thus, missing tobacco abstinence outcomes will not be imputed. To control for false discovery, the selection of model terms will generally be guided by the adjusted *p*-values by using the method of Benjamini and Yekateuli (2001) [63] for dependent false discovery rate because there may exist plausible correlations in the *p*-values between the main effects and the interaction terms.

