**Methods:**

The Cessation and Screening to Save Lives (CASTL) trial seeks to advance knowledge about the reach, effectiveness, and implementation of tobacco treatment in lung cancer screening. We describe the rationale, design, evaluation plan, and interventions tested in this multiphase optimization strategy trial (MOST). A total of 1152 screening-eligible current smokers are being recruited from 18 LCS sites (*n* = 64/site) in both academic and community settings across the USA. Participants receive enhanced standard care (cessation advice and referral to the national Quitline) and are randomized to receive additional tobacco treatment components (motivational counseling, nicotine replacement patches/lozenges, message framing). The primary outcome is biochemically validated, abstinence at 6 months follow-up. Secondary outcomes are self-reported smoking abstinence, quit attempts, and smoking reduction at 3 and 6 months. Guided by the Implementation Outcomes Framework (IOF), our evaluation includes measurement of implementation processes (reach, fidelity, acceptability, appropriateness, sustainability, and cost).

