#### Baseline variables

Our baseline assessment includes measurement of demographic characteristics (age, gender, race, ethnicity, education, marital status, education, and SES), perceived health risks (personal and comparative), worry about lung cancer, current and smoking history (frequency, number of cigarettes smoked, age of the first cigarette and current use (in the past 30 days) of other tobacco products including e-cigarettes). We also assess participants’ health literacy, self-reported physical health, medical comorbidities, family history of lung cancer, behavioral health (depression, alcohol, and illicit drug use), smoking cessation beliefs (readiness and confidence to quit, importance of quitting, and attitudes about NRT and stigma). We also added an assessment of changes in motivation and rates of smoking resulting from the COVID-19 pandemic. This collection of variables will allow us to characterize the sample and investigate moderators of treatment outcomes.

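### The primary abstinence model names no baseline covariate although suitable pre-randomization measures are collected; the analysis is valid, but prespecified adjustment would be a small, nearly free gain

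*Protocol article*

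**What the plan says.** Under 'Analytic strategies to address research aims', the article sets out the Aim 1 analysis: a generalized mixed model with a logit link, random intercepts for site, and factorial fixed effects, where "a fully saturated model includes all four main component effects, 6 two-way interactions, 4 three-way interactions, and 1 four-way interaction". Terms are then kept or dropped by p < 0.05, guided by Benjamini-Yekutieli adjusted p-values. Missing outcomes count as non-abstinent. No baseline covariate is mentioned.

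Table 2 and 'Baseline variables' list cigarettes per day, the Heaviness of Smoking Index, readiness to quit and confidence among the baseline measures. The survey is completed before randomization. The stated purpose is: "This collection of variables will allow us to characterize the sample and investigate moderators of treatment outcomes". Adjustment of the primary comparison is not among the uses.

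Three other statements bear on the point:
- Randomization is stratified by site only.
- Participants who do not complete the baseline assessment are removed ('Criteria for removal and adverse events'), so these measures should be nearly complete.
- 'Trial status and modifications' reports 734 enrolled at the time of writing and concedes that 1152 will not be reached.

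**The concern.** In a logistic analysis, a covariate that predicts the outcome can raise the power of the treatment test, provided it is measured before randomization and prespecified. This trial has such candidates in hand at no further cost, yet the described model does not use them. The power statement was built on 1152 participants, so any efficiency left unused matters somewhat more now that the sample will be short. Timing matters too. Analysis starts only after data collection ends, and the article says the data analysts are not blind to assignment. Covariates chosen after outcomes have been seen would carry little credibility.

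**Working it through.** **Inputs from the documents.** N = 1152 ("A total of 1152 screening-eligible current smokers are being recruited from 18 LCS sites"); type I error two-sided 5%; "estimated minimal effect size of 0.20 in standard deviation units"; "accounting for up to 20% attrition"; illustration: "a difference between 20 and 12% abstinence rates, when converted by an arcsine transformation"; 734 enrolled so far. Each main effect compares half the sample with half (Table 1, equal allocation assumed).

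**Input not in the documents.** The prognostic strength of the baseline measures. It is assumed below and shown as a range.

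**Step 1: reproduce the planned figure.** Power ≈ Φ(d·√(n/2) − 1.96), with n per level.
- n = 1152 × 0.8 / 2 = 460.8: 0.20 × √230.4 = 3.04, so power is 85.9%. The article says the sample "will afford an 85% statistical power", so the figure reproduces.
- The arcsine difference for 20% and 12% is 0.220, as stated.

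**Step 2: the shortfall, unadjusted.** If accrual stopped at 734:
- All 734 counted: n = 367, 0.20 × √183.5 = 2.71, power 77.3%.
- Less 20% (587): 0.20 × √146.8 = 2.42, power 67.8%.

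**Step 3: what adjustment is worth by formula.** A covariate score explaining a share R² of outcome variance acts like a sample of N/(1 − R²).

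| Effective base N | R² = 0 | 0.02 | 0.05 | 0.10 | 0.20 |
|---|---|---|---|---|---|
| 922 | 85.9% | 86.6% | 87.6% | 89.3% | 92.4% |
| 734 | 77.3% | 78.1% | 79.4% | 81.5% | 85.8% |
| 587 | 67.8% | 68.7% | 70.1% | 72.4% | 77.3% |

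In participants, R² = 0.05 at N = 734 is worth 734/0.95 − 734 ≈ 39 people. In simulation at 12% vs 20%, an AUC of 0.64 corresponded to R² of about 0.03, an AUC of 0.70 to about 0.06, and an AUC of 0.75 to about 0.10.

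**Step 4: simulation with a binary outcome.** Scoring 20% missing as non-abstinent dilutes 20% vs 12% to 0.8 × 20 = 16% vs 0.8 × 12 = 9.6%. Two runs, each of 4000 trials per setting, tested one contrast by logistic regression with and without one standardized covariate (no site effect, interactions or false-discovery adjustment).

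First run, by log-odds per SD of the covariate:

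| Log-odds per SD | N = 734 | N = 800 |
|---|---|---|
| 0 | 73.3 → 73.3% | 78.1 → 78.0% |
| 0.4 | 73.4 → 73.6% | 77.5 → 77.8% |
| 0.6 | 75.2 → 76.5% | 76.4 → 78.3% |
| 0.8 | 74.3 → 77.4% | 76.9 → 80.0% |
| 1.0 | 73.9 → 78.4% | 77.4 → 81.4% |

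Second run, gain in points at N = 734 and N = 800: 0.2 and 0.4 (AUC 0.59), 1.4 and 1.4 (AUC 0.64), 2.4 and 2.0 (AUC 0.67), 2.5 and 2.6 (AUC 0.71). An uninformative covariate gave −0.2 at both sizes, within simulation noise.

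**Step 5: the more favourable case.** With the undiluted 12% vs 20% at N = 736 (3000 trials per setting), unadjusted power is already about 84 to 86%. Adjustment moves it from 84.2 to 84.5% (odds ratio 1.35 per SD), 85.4 to 86.3% (1.65), 85.3 to 87.4% (2.12) and 85.7 to 89.5% (2.72).

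**The case against.** **The article is a condensed document.** The sentence on the saturated model counts factorial terms; it does not close the list of covariates. The sentence on baseline variables states a use and forbids nothing. A reader might infer that covariates have been ruled out, but the text does not say so, and the full protocol or an analysis plan may add them. What stands is narrower: the article sets out link, clustering, fixed effects and selection rule, assigns the baseline data a different purpose, and never names adjustment.

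**Nothing is invalid.** A reader might infer that the unadjusted odds ratios are biased toward 1. They are not. The adjusted and unadjusted odds ratios differ because odds ratios are non-collapsible; the unadjusted one targets the marginal effect, and the unadjusted test keeps its type I error. Site, the only stratification factor, is already in the model. This objection stands in full.

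**Strong predictors and rescued power.** Both are tempting readings. No part of the article gives prognostic strength, and at the assumed strengths adjustment does not make up for missed accrual.

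**Imbalance across 16 small conditions.** At N = 734 a condition holds about 734/16 ≈ 46 people, but each main effect compares 367 with 367. The standard deviation of a chance covariate difference there is √(2/367) ≈ 0.07 SD, which the standard error already covers.

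**A single test at 5% is not the planned decision rule.** This is correct. For one lone effect among 15 terms, the Benjamini-Yekutieli threshold is about 0.05/(15 × 3.32) = 0.001. For 16% vs 9.6% at N = 734, z ≈ 0.064/0.0247 ≈ 2.60 against a critical value of 3.29, so power is about 24%. With R² = 0.05, z becomes 2.60/√0.95 ≈ 2.66 and power about 27%. The power levels in the working therefore do not describe the final selection step, although the rough gain there is of similar size.

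**Conclusion.** The point holds as a modest efficiency recommendation. The primary model as described (15 factorial terms plus a random site intercept) names no baseline covariate, while suitable measures are collected before randomization and should be nearly complete. The gain is about 0 to 3 power points for one main-effect contrast at two-sided 5% and N = 734 to 800, under assumed AUCs of about 0.6 to 0.71. It reaches 4 to 5 points only for a stronger score (R² near 0.10), and there is no material loss if the score is uninformative. For the planned effect of 0.20, adjustment returns power to 85% at N = 734 only near R² = 0.20 with every participant counted (85.8%), and not at 587 even then (77.3%).

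The result rests on the assumed prognostic strength and on 734 to 800 as the final size. The article gives no final N; 734 is enrolment at the time of writing, so the shortfall may be smaller. Because missing outcomes are scored as non-abstinent, figures that simply remove 20% of participants are approximate.

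**What to change.** In 'Analytic strategies to address research aims', before outcome data are analysed:
- Prespecify a short fixed list of baseline covariates for the primary mixed logistic model: the Heaviness of Smoking Index (or cigarettes per day), readiness to quit, and confidence to quit.
- State that they are always kept and are exempt from the p < 0.05 and false-discovery selection, which applies to the factorial terms only.
- Report standardized (marginal) abstinence differences alongside the conditional odds ratios, so that the effect can be read on the marginal scale.

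If the full protocol or an analysis plan already names covariates, it is enough for the article to say so and to align the statement of purpose under 'Baseline variables'. The cost is two or three sentences and a routine standardization step; no new data, participants or site work are needed.
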